## Abstract

**Background:**

IUGR infants are thought to have impaired gut function after birth, which may result in intestinal disturbances, ranging from temporary intolerance to the enteral feeding to full-blown NEC.

In literature there is no consensus regarding the impact of enteral feeding on intestinal blood flow and hence regarding the best regimen and the best rate of delivering the enteral nutrition.

**Methods/design:**

This is a randomized, non-pharmacological, single-center, cross-over study including 20 VLBW infants.

Inclusion criteria

* Weight at birth ranging: 700–1501 grams

* Gestational age up to 25 weeks and 6 days

* Written informed consent from parents or guardians

Exclusion criteria

* Major congenital abnormality

* Patients enrolled in other trials

* Significant multi-organ failure prior to trial entry

* Pre-existing cutaneous disease not allowing the placement of the NIRS’ probe

In the first 24 hours of life, between the 48^th^ and 72^nd^ hours of life, and during Minimal Enteral Feeding, all infants’ intestinal perfusion will be evaluated with NIRS and a Doppler of the superior mesenteric artery will be executed.

At the achievement of an enteral intake of 100 mL/Kg/day the patients (IUGR and NON IUGR separately) will be randomized in 2 groups: Group A (n=10) will receive a feed by *bolus* (in 10 minutes); then, after at least 3 hours, they will receive the same amount of formula administered in 3 hours. Group B (n=10) will receive a feed administered in 3 hours followed by a *bolus* administration of the same amount of formula (in 10 minutes) after at least 3 hours.

On the randomization day intestinal and cerebral regional oximetry will be measured via NIRS. Intestinal and celebral oximetry will be measured before the feed and 30 minutes after the feed by *bolus* during the 3 hours nutrition the measurements will be performed before the feed, 30 minutes from the start of the nutrition and 30 minutes after the end of the gavage. An evaluation of blood flow velocity of the superior mesenteric artery will be performed meanwhile. The infants of the Group A will be fed with continuous nutrition until the achievement of full enteral feeding. The infants of the Group B will be fed by *bolus* until the achievement of full enteral feeding.

**Discussion:**

Evaluations of intestinal oximetry and superior mesenteric artery blood flow after the feed may help in differentiating how the feeding regimen alters the splanchnic blood flow and oxygenation and if the changes induced by feeding are different in IUGR versus NON IUGR infants.

**Trial registration number:**

NCT01341236

## Background

Intra-uterine growth restriction (IUGR) caused by placental insufficiency is characterized by blood flow redistribution to the vital organs (brain, myocardium, and adrenal glands), while other organs, including the gastrointestinal tract, are deprived from sufficient blood flow. As a consequence of gut ischemia/hypoxia, IUGR infants are thought to have impaired gut function after birth, which may result in intestinal disturbances, ranging from temporary intolerance to the enteral feeding to full-blown NEC.

In literature, however, there is no consensus regarding the impact of enteral feeding on intestinal blood flow and hence regarding the best regimen and the best rate of delivering the enteral nutrition.

Doppler ultrasonography is the method currently used for the clinical assessment of velocity of superior mesenteric artery blood flow [1]. Blood flows parameters in the superior mesenteric artery (SMA) change with vasoconstriction or vasodilatation of the intestinal vascular bed. Prenatal utero-placental insufficiency with chronic fetal hypoxia can lead to foetal growth retardation with a redistribution of blood flow favouring the cerebral circulation and reducing mesenteric perfusion [2]. This underlines the importance of chronic or acute hypoxia as the most intensively studied condition associated with disturbances of intestinal motility.

The possible association between the increase in blood flow velocity and change in tissue oxygenation is expected. Greater understanding of the rate of oxygen delivery and uptake in sick preterm infants undergoing intensive care is an important aim of neonatal medicine.

The assessment of adequate perfusion in very low birth weight infants is commonly based on clinical parameters, as well as invasive measures requiring central venous and/or arterial catheter access with well established associated risks. Additionally, most of these data are acquired intermittently, and thus may only represent a delayed picture of oxygen delivery and consumption.

Near-infrared spectroscopy (NIRS) is a continuous, non-invasive, real-time and portable techinique, which can be used to measure oxygenation in living tissue [3].

In 1985, Brazy and Lewis [4] reported the first pediatric application of NIRS monitoring of cerebral oxygenation in sick preterm infants. Since then the list of publications on NIRS for hemodynamic and oxygenation assessment in children and adults has rapidly expanded [5,6].

The technological background of NIRS technology has been reviewed in detail [7]. The main principle upon which NIRS device relies is the fact that most biological tissues, other than haemoglobin and cytochrome oxidase, are relatively transparent to infrared light in the range closest to the visual spectrum (700–1000 nanometers), and that the absorbance spectrum of the haemoglobin depends on its oxygenation status (deoxygenated haemoglobin absorbs more red light and less infrared light than oxygenated haemoglobin). All devices emit lights at wavelengths within the above mentioned spectrum and analyze photons returning to the transducer. Because the change in the intensity of the reflected light is dependent upon the oxyhemoglobin to deoxyhemoglobin ratio, oxyhemoglobin saturation can be derived [8]. There are many different NIRS devices available. We use the INVOS cerebral oximeter (Somanetics Corporation, Troy, Michigan USA) that is FDA approved for adult and pediatric use including infants [9].

NIRS has been used to monitor oxygenation of the brain in neonates by measuring the ratio of oxygenated to deoxygenated hemoglobin (termed “tissue oxygenation index”, TOI) [10]. NIRS has been reported to be useful in detecting changes in splanchnic oxygen delivery and predicting splanchnic ischemia in neonates by measuring the ratio of splanchnic to cerebral TOI, the cerebrosplanchnic oxygenation ratio (CSOR). Splanchnic oxygenation is compared with brain oxygenation as a reference, because under most of physiological conditions cerebral blood flow autoregulation minimizes changes in brain oxygenation during events affecting splanchnic perfusion [11].

A significant concern with the application of NIRS to the abdomen is the possibility of movement of the gut within the abdomen and also movement produced by peristalsis of the gut wall. These two movements can alter the scattering path of the near infrared light, resulting in absorption changes, which would swamp the signal of interest [12,13]. However TOI now offers a method of comparing the haemoglobin redox status within the splanchnic circulation, which is not path-length-dependent because it provides a simultaneous ratio of oxyhaemoglobin to deoxyhaemoglobin. Finally, by measuring the TOI of the brain, which is preferentially autoregulated with the splanchnic region under most physiological conditions, the resultant CSOR ratio gives absolute values, which allow comparison between individual patients. CSOR had a 90% (56-100%) sensitivity to detect splanchnic ischaemia in neonates [14].

Regional tissue oxygenation of some other vascular beds and its clinical relevance is under review in extremely low birth weight infants [15].

In an effort to decrease the risk for development of NEC in preterm infants, enteral nutrition is often delayed when the neonate shows signs of feeding intolerance. However, enteral fasting can predispose a neonate to impaired intestinal growth, mucosal atrophy, intestinal barrier dysfunction, decreased digestive and absorptive capacity, increased colonization with pathogenic bacteria, and systemic inflammation. In addition, enteral fasting can prolong the time to establish full enteral feeding and the length of hospital stay [16]. Consequently, minimal enteral feeding (MEF) in combination with parenteral nutrition (PN) is often employed to alleviate the side effects of enteral fasting in premature infants. MEF is thought to promote intestinal motility, to maintain the intestinal barrier, to stimulate the development of “good” microflora, and to reduce infections.

Tube feeding is necessary for most premature infants less than 1500 grams because of their inability to coordinate sucking, swallowing, and breathing and the risk of aspiration. The conventional tube feeding method is intermittent bolus gavage feeding, where a prescribed volume of milk is given over a short period of time, usually over 10 to 20 minutes by gravity. Some clinicians prefer the continuous nasogastric route to feed premature infants less than 1500 grams birth weight, although, in practice, intermittent bolus gavage feeding is the method more commonly used [17,18]. In our Unit VLBW infants are fed by boluses, although they are often empirically switched to the continuous infusion method without an established rationale. Theoretical risks and benefits of both continuous nasogastric milk feeding and intermittent bolus milk feeding have been proposed. Continuous nasogastric feedings may improve energy efficiency (by increasing energy absorbed and decreasing energy expenditure), reduce feeding intolerance, improve nutrient absorption, and improve growth. However, continuous infusion of milk into the gastrointestinal tract could alter the cyclical pattern of release of gastrointestinal tract hormones, which might affect metabolic homeostasis, and growth. Milk feedings given by bolus gavage method are thought to be more physiologic because they promote the cyclical surges of gastrointestinal tract hormones normally seen in healthy term infants. On the other hand, functional limitations of the premature infant’s gastrointestinal system such as delayed gastric emptying or intestinal transit could hinder the premature infant’s ability to handle bolus milk feeds, resulting in feeding intolerance.

Additionally, this feeding regimen that alternates between periods of feeding and fasting may challenge the premature infant’s ability to maintain metabolic homeostasis and, therefore, decrease growth. There is still a debate about which is the best feeding regimen in order to prevent episodes of feeding intolerance and to promote a better growth.

### Aims of the study

Primary aim of this study:

1. To evaluate the changes in the intestinal perfusion and oximetry determined by feeding in VLBW infants fed by 3 hours nasogastric nutrition (CN) *versus* infants fed by bolus nutrition (BN).

Secondary aims of the study:

2. To compare if changes in the intestinal perfusion and oximetry induced by feeding are different between IUGR and NON-IUGR infants.

3. To compare growth and nutritional status of the 2 groups by randomized arm.

4. To test if changes in intestinal oximetry and perfusion can be reliable predictors of feeding intolerance (days necessary to achieve full enteral feeding)*.*

### Endpoints

The endpoint for the primary aim will be the cross-over difference of CSOR values, measured with NIRS before and at the end of the randomized feeds.

Aims 1 to 4 will be pursued analysing the following endpoints:

· The cross-over difference of CSOR values and of rSO2s values (i.e. the splanchnic saturation slope) in IUGR and non-IUGR infants.

· Growth and nutritional status will be measured by weight, length and head circumference. Main comparison will be between measures at randomization and at achievement of full enteral feeding. The growth at 28 days of life and at 36 weeks of gestational age will also be compared with the appropriate standard growth curves.

· The difference in the CSOR values pre- and post- feeding will be compared with the baseline CSOR value and the baseline Doppler flow velocimetry (both measured within the first 72 hours of life)*.*

· Comparison of the time needed to reach full enteral feeding (i.e. days from randomization till enteral intake of 160 ml/kg/day of formula or fortified human milk) by randomized arm;

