#### Statistical analysis

The primary aim of the study is to compare the impact on intestinal perfusion of 2 different nutrition modalities, bolus (BN, Group A) versus a 3-hour nasogastric nutrition (CN, Group B). The impact on intestinal perfusion is defined as the difference between pre- and post-prandial CSOR values measured with NIRS 30 minutes before feeding and at the expected peak after feeding (3 hours in CN and 30 minutes in BN). Pre- and post-prandial CSOR values will be calculated as the mean of 5-minute NIRS evaluations about the intended time-point (e.g. for baseline CSOR measurement, 2.5 minutes before and 2.5 minutes after the 30th minute before start of the randomized feed). Given that the study is a cross-over study, each infant will be evaluated both for CN and BN and the cross-over CSOR difference will be the primary endpoint.

As a secondary analysis, the cross-over difference of CSOR values as well as that of SO2s values (i.e. the splanchnic saturation slope) will be analysed comparing intra-uterine growth (IUGR vs. non-IUGR).

The impact of the 2 nutrition modalities on CSOR will also be studied in a multivariable context, adjusting for factors including the baseline CSOR value, the baseline Doppler flow velocimetry (both measured within the first 72 hours of life) and the intra-uterine growth (IUGR vs. non-IUGR).

Other secondary analyses include:

· Comparison of the time needed to reach full enteral feeding (i.e. days from randomization till enteral intake of 160 mL/Kg/day of formula or human milk) by randomized arm;

· Comparison of growth as measured by weight, length and head circumference by randomized arm. Main comparison will be between measures at randomization and at achievement of full enteral feeding. The growth at 28 days of life will also be compared with the appropriate standard growth curves.

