The primary end-point analysis as well as all secondary analyses regarding randomized patients will be based on the ITT (intention-to-treat) principle. Comparisons of the two arms accounting for deviations from the assigned arm (analyses by “performed treatment”) will also be added to this main analysis. The primary endpoint will be analyzed with a two-tailed matched pairs t-test, after checking of appropriateness of assumptions. In particular, checking will concern the normality assumption, since period effect and cross-over effect appear both very unlikely in this study. Should normality be not adequate, non-parametric test such as the Wilcoxon signed ranks test will be applied [20]. An appropriate generalized linear model will be used to investigate the relationship between the CSOR cross-over difference and the candidate covariates. Should any raw CSOR observations be missing (e.g. NIRS instrument failed to measure or to save measurements), their estimation via imputation or other appropriate methods will be taken into account. The comparison of growth variables by randomized arm will be performed with either the two-tailed t-test or a non-parametric alternative (e.g. Mann–Whitney test), should the normality assumption be not reasonable. The time from randomization till achievement of the full enteral feeding will be analysed with the Kaplan-Meier estimator, in which full enteral feeding as defined in the protocol will be considered as the sole ‘event’, while censoring will occur for withdrawal for any cause. Standard errors will be computed according to Greenwood formula and the log-rank test will be used for univariate comparisons.

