### Sample size

This single-center study will recruit patients for 2 years (24 months) since official opening. The expected accrual is about 20 VLBW infants, either IUGR or non-IUGR. The power calculations below are based on a two-tailed t-test with I-type error α=0.05 and show the power that the 20-patient study will achieve under various differences in CSOR from the ‘baseline’ impact observed under BN. On the basis of previous studies [21] this is expected to be 0.10 (mean of CSOR pre-post prandial difference), while various hypothesis are made about its standard deviation, σ_CSOR_

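### The endpoint relating the feed-induced CSOR change to the first-72-hour baselines has no clearly matching model: the only covariate model with a named response uses the cross-over difference, from which a dependence shared by both feeds cancels

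*Protocol article*

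**What the plan says.** The Endpoints section separates two quantities. For the primary aim, "The endpoint for the primary aim will be the cross-over difference of CSOR values". A later bullet is a separate endpoint: "The difference in the CSOR values pre- and post- feeding will be compared with the baseline CSOR value and the baseline Doppler flow velocimetry", with these baselines coming from the first 72 hours of life.

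Statistical analysis keeps the same distinction. "The impact on intestinal perfusion is defined as the difference between pre- and post-prandial CSOR values", which is a change within one feed. The contrast between feeds is then introduced: "each infant will be evaluated both for CN and BN and the cross-over CSOR difference will be the primary endpoint".

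Two sentences bear on covariates:

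- "The impact of the 2 nutrition modalities on CSOR will also be studied in a multivariable context, adjusting for factors including the baseline CSOR value"; further adjustment factors named there are baseline Doppler and intra-uterine growth.
- "An appropriate generalized linear model will be used to investigate the relationship between the CSOR cross-over difference and the candidate covariates".

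The list of other secondary analyses covers only time to full enteral feeding and growth.

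**The concern.** The endpoint asks whether an infant's early splanchnic oxygenation and mesenteric flow are related to how CSOR changes with a feed. The model with a named response asks something else: whether the difference between the two feeds varies with the covariates. An infant whose early perfusion predicts a small response to both feeds contributes nothing to that second question.

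At stake is a secondary endpoint close to the rationale in the Background and Discussion, which link reduced gut perfusion to feeding tolerance. The multivariable analysis is also the only analytic use that the statistical section states for the NIRS and Doppler recordings of the first 72 hours. If its response is the cross-over difference, it cannot show a relation that holds equally under both modes of feeding.

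**Working it through.** **The plan's own figure.** Table 1 gives powers for 20 infants, "based on a two-tailed t-test with I-type error α=0.05". For a paired t-test with 19 degrees of freedom and non-centrality (difference / SD) × √20:

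| SD | Difference | Non-centrality | Power computed | Power stated |
|---|---|---|---|---|
| 0.10 | 0.07 | 3.13 | 84.4% | 84% |
| 0.15 | 0.10 | 2.98 | 80.7% | 80% |
| 0.20 | 0.13 | 2.91 | 78.7% | 78% |

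The table reproduces when its SD is taken as that of the cross-over difference. It therefore does not fix the SD of the change within a single feed, which the next steps need.

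**Algebra.** Let x be a baseline, and let the changes under bolus (B) and continuous (C) feeding be

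- Y_B = a_B + b_B·x + e_B
- Y_C = a_C + b_C·x + e_C

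Then Y_B − Y_C = (a_B − a_C) + (b_B − b_C)·x + (e_B − e_C).

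The slope in the stated model is b_B − b_C. If b_B = b_C = b, it is zero for any b. The infant's mean change, (Y_B + Y_C)/2, has slope (b_B + b_C)/2, which equals b in that case. The direction of the difference is not given in the article and does not matter.

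**Simulation.** From the article: n = 20, two-sided α = 0.05. Assumed, because the article gives no values: a standardised baseline, a common slope of 0.05 CSOR per baseline SD, the residual SD σ of the change within one feed, and the correlation ρ between an infant's two residuals. There is one baseline covariate per regression. The residual SD of the mean change is σ·√((1+ρ)/2); that of the cross-over difference is σ·√(2(1−ρ)).

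| σ per feed | ρ | Residual SD of mean change | Cross-over-difference model rejects | Mean-change regression rejects |
|---|---|---|---|---|
| 0.10 | 0 | 0.071 | 5% | 80% |
| 0.10 | 0.5 | 0.087 | 5% | 64% |
| 0.15 | 0 | 0.106 | 5% | 48% |
| 0.15 | 0.5 | 0.130 | 5% | 35% |
| 0.20 | 0 | 0.141 | 5% | 31% |
| 0.20 | 0.5 | 0.173 | 5% | 22% |

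At ρ = 0.5 the SD of the difference equals σ, so those three rows match Table 1's SDs as reproduced above. If instead the feeds are independent and the SD of the difference is 0.10, then σ = 0.10/√2 = 0.071 and the mean-change regression has 96% power.

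The slope matters as much. With σ = 0.10 and ρ = 0, power is 41% at a slope of 0.03 and 96% at 0.07. With σ = 0.20, ρ = 0.5 and a slope of 0.03 it is 11%. The cross-over-difference model stays at about 5% throughout.

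**What the stated model can detect.** With unequal slopes and independent residuals of SD 0.071 per feed, it rejects in 53% of trials for slopes 0.05 and 0, and in 23% for 0.05 and 0.02. It does test effect modification, with modest power.

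**The case against.** The best counter-argument lies in the article's own definition. *Impact* is defined as the change within a feed, and the sentence that names the baselines says that impact will be studied adjusting for them. Read alone, this could describe a model of the per-feed change on modality and baselines, which would contain the slope the endpoint asks about. The model sentence that follows speaks only of candidate covariates and does not name the baselines. A reader might infer that the baselines certainly enter only a cross-over-difference model, and that the endpoint therefore goes untested. The document does not settle that. What stands is that the multivariable sentence treats the baselines as adjusters of the modality comparison, and the only response named for a covariate model is the cross-over difference. The two sentences need reconciling.

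Further points on the other side:

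- None of the four listed aims asks directly whether early perfusion determines the feeding response, and effect modification is a fair question under the first aim. True, but the Endpoints section still lists the relation as an endpoint of its own.
- An article may leave a secondary model to the analysis plan. That would answer a complaint of missing detail; here a response is named and it does not match the endpoint.
- A reader might infer that a null result would be reported as no relation with early perfusion, or that a change is literally to be compared with a velocity. The article states no such interpretation, and the comparison wording plainly means *related to*.
- The advantage of a matching model is easily overstated. A contrast of 80% with 5% is the favourable setting among the per-feed SDs of 0.10 to 0.20 tabulated, and a model with five predictors in 20 infants would not reach the power of a single-covariate regression.

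**Conclusion.** The point holds as a mismatch between a listed secondary endpoint and the response of the only fully named covariate model, with an ambiguous sentence between them. On the joint reading, the stated model tests b_B − b_C and has no power beyond the 5% error rate for a dependence common to both feeds. That follows from algebra and needs no assumption about SD or correlation.

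The benefit of correcting it does rest on assumptions. At a slope of 0.05 per baseline SD, the mean-change regression has between 22% and 80% power over per-feed SDs of 0.10 to 0.20 and correlations of 0 to 0.5. The matching model asks the right question; with 20 infants it will not always answer it. The Discussion describes the study as explorative and the endpoint is secondary, so this is a worthwhile clarification and not a threat to the main result.

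**What to change.** State under Statistical analysis that, for this endpoint, the response is the pre/post CSOR change within a feed. Either form will do:

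1. Regress each infant's mean change over the two feeds on each baseline in turn: baseline CSOR, then one prespecified index from the Doppler examination.
2. Fit a model with two rows per infant, containing modality, baseline and baseline-by-modality, with a random infant intercept. With modality coded symmetrically (for example −½ and +½), the baseline main slope answers the endpoint and the interaction addresses effect modification.

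Keep the existing cross-over-difference model and label it as the test of whether a covariate modifies the bolus-versus-continuous contrast. Reword the multivariable sentence so that its response is explicit.

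The cost is one more exploratory model on data already planned, with no new measurements or infants. Covariates must be kept few because n = 20, and the result should be reported as an estimate with its confidence interval.
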